**Methods/design:**

A pragmatic, cluster randomized trial conducted within a clinical network of 12 Kenyan county referral hospitals providing inpatient pediatric care to children (aged 2–59 months) with acute medical conditions between March and November 2016. The intervention comprised enhanced feedback (monthly written feedback incorporating goal setting, and action planning delivered by a senior clinical coordinator for selected pneumonia indicators) and this was compared to standard feedback (2-monthly written feedback on multiple quality of pediatric care indicators) both delivered within a clinical network promoting clinical leadership linked to mentorship and peer-to-peer support, and improved use of health information on service delivery. The 12 hospitals were randomized to receive either enhanced feedback (*n* = 6) or standard feedback (*n* = 6) delivered over a 9-month period following nationwide pneumonia treatment policy change. The primary outcome is the proportion of all admitted patients with pneumonia (fulfilling criteria for treatment with orally administered amoxicillin) who are correctly classified and treated in the first 24 h. The secondary outcome will be measured over the course of the admission as any change in treatment for pneumonia after the first 24 h.

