
### Sample size

Based on the primary outcome of correct pneumonia classification and treatment we performed a power calculation to determine the feasibility of conducting the trial within the period of the network’s funding cycle using a fixed number of hospitals recruited into CIN. Using data collected during the first year of CIN operation we determined that: on average, 616 (range 310–898) children are admitted to each hospital annually with pneumonia and of these 150 children (range 78–228) are eligible for treatment with amoxicillin. We estimated that if we evaluate the primary outcome 9 months after trial commencement with six hospitals per arm then at least 680 patients with pneumonia requiring amoxicillin treatment will be enrolled per arm. Assuming an average cluster size of 113 patients and an intracluster correlation coefficient (ICC) of 0.2 (corresponding to a variance inflation factor (VIF) of 15.8 and based on calculation of pneumonia classification and treatment within CIN hospitals), a Type-I error rate of 5%, and 90% power we will be able to detect a two-fold increase in the odds of correct pneumonia classification and treatment over 9 months if correct pneumonia classification and treatment is 30% in the control group following the treatment policy change. To ensure that the desired sample size is attained within each hospital, all eligible patients will be recruited in the hospitals with a workload less than 3000 annual pediatric admissions. For hospitals with a very high annual workload (at least 4000 admissions) a random sample will be selected using computer-generated random numbers applied to eligible participants.

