#### Statistical methods

Characteristics of patients and hospitals in the analysis will be compared according to treatment arm to evaluate the ability of randomization to deliver balance across hospital groups. Any variables that show imbalance between intervention groups will be considered for adjustment in comparison of intervention effect.

The primary comparison of correct classification and treatment of pneumonia will include all patients meeting clinical criteria for pneumonia (but not severe pneumonia) recruited in the trial during the 9-month period. The primary outcome will be a binary variable indicating whether a child admitted with non-severe pneumonia is correctly classified and treated based on new guideline recommendations. To account for the cumulative effect of feedback delivered at different time points during the 9-month intervention, the primary comparison will be adjusted for time between commencement of intervention and patient recruitment. A hierarchical logistic regression analysis will be conducted with the primary outcome (correct pneumonia classification and treatment) and independent variables including treatment arm, time (as a continuous variable), and both patient level and hospital level and adjusting for any imbalances in patient characteristics. The model will account for clustering by including a random effect for hospital. The change in performance over time will be included as a time trend. Tests for significant differences in the time trend between the treatment arms will be examined by including an interaction term between the treatment group and the time variable.

In separate sensitivity analysis, multiple imputation will be used to handle missing data and allow classification of all pneumonia patients. Bayesian bootstrap predictive mean matching will be conducted 50 times to impute missing data for signs required to classify pneumonia severity. After imputation, diagnostic checks will be conducted to compare the distribution of imputed and observed data. The modeling approaches used in the primary trial analysis will be repeated after imputation on each imputed dataset and the estimates combined using Rubin’s rules.

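### The arm-by-time test has one stated hospital random effect and no hospital slope, so its standard error is too small if hospitals take up the policy at different speeds

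*Protocol article*

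**What the plan says.** All of the model text is in the protocol article, Statistical methods.

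- Primary comparison: "the primary comparison will be adjusted for time between commencement of intervention and patient recruitment". The stated reason is "To account for the cumulative effect of feedback delivered at different time points during the 9-month intervention".
- Covariates: "independent variables including treatment arm, time (as a continuous variable"), plus patient-level and hospital-level variables. The interaction is not in this list.
- Clustering: "The model will account for clustering by including a random effect for hospital". No other clustering term is named.
- Trend test, stated afterwards: "Tests for significant differences in the time trend between the treatment arms will be examined by including an interaction term" of treatment group with time.

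The article names no hospital-specific time slope. It does not say whether the interaction stays in the model that supplies the reported arm effect.

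On the design, the abstract says "The 12 hospitals were randomized to receive either enhanced feedback" or standard feedback, six hospitals in each arm. The Sample size section gives the planning inputs: "Assuming an average cluster size of 113 patients and an intracluster correlation coefficient (ICC) of 0.2 (corresponding to a variance inflation factor (VIF) of 15.8").

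**The concern.** The hospital is the unit of randomization, so any contrast between arms, in level or in trend, carries hospital-to-hospital variation. A single random effect per hospital absorbs differences in level. It does nothing for differences in slope. When the interaction is added to that model, all hospitals within an arm are treated as sharing one slope, and hundreds of patients per arm stand in for six hospitals per arm.

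Different speeds of uptake are plausible. The trial starts at a change of national policy, and the Participants section describes clusters that differ in region, morbidity and workload. At stake is a statement that enhanced feedback sped up adoption, or failed to, with a p-value and interval that look more precise than they are.

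A second point is conditional. Time runs from commencement, so once the interaction is in the model the arm coefficient no longer describes the whole nine months.

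**Working it through.** **Plan's own figure.** There is none for the trend test, so there is nothing to reproduce. The stated cluster size and ICC serve only to set the scale. (They give 1 + 112 × 0.2 = 23.4, not the stated 15.8. That is a separate matter and does not enter here.)

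**Inputs from the article.** 12 hospitals, six per arm; mean 113 eligible patients per hospital; ICC 0.2; nine months; annual eligible patients per hospital from 78 to 228, used to make cluster sizes unequal.

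**Assumptions.** ICC on the latent logistic scale, so the intercept SD is √(0.2/0.8 × π²/3) = 0.91. A common upward trend of 0.10 log-odds per month. Hospital slopes independent of intercepts, with an assumed SD. No arm effect and no arm-by-time effect. Two-sided 5%.

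**Expected direction.** Let b3 be the arm-by-time coefficient and τ the between-hospital slope SD. Then, roughly,

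Var(b3) ≈ V0 + τ²(1/6 + 1/6) = V0 + τ²/3,

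where V0 is the variance when slopes do not vary. A random-intercept model reports a standard error close to √V0 whatever τ is. With τ = 0 the simulated SD of the estimate is 0.0514. At τ = 0.10 the formula gives √(0.0514² + 0.10²/3) = 0.077; the simulation below gives 0.080.

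**Simulation.** 1,000 trials per value of τ. The model was fitted as stated, by maximum likelihood with a random intercept and a Wald z test of arm × time. For comparison, a slope was fitted in each hospital and the 12 slopes were compared by t-test on 10 degrees of freedom.

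| τ, log-odds per month | τ × 9 | True SD of b3 | Mean model SE | False positives, random intercept | False positives, slope t-test |
|---|---|---|---|---|---|
| 0 | 0 | 0.051 | 0.050 | 5.3% | 5.4% |
| 0.03 | 0.27 | 0.053 | 0.050 | 5.7% | 3.2% |
| 0.05 | 0.45 | 0.059 | 0.050 | 8.7% | 4.2% |
| 0.10 | 0.90 | 0.080 | 0.051 | 21.9% | 4.9% |
| 0.15 | 1.35 | 0.097 | 0.052 | 29.6% | 4.5% |
| 0.20 | 1.80 | 0.118 | 0.053 | 36.8% | 4.2% |

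The Monte Carlo standard error is about 0.7 points near 5% and 1.5 points near 37%. The mean of b3 lies between −0.004 and 0.002 throughout, so the estimate is not biased.

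**Cross-check.** The false-positive rate should be near 2 × [1 − Φ(1.96 × SE/SD)]. At τ = 0.10: 1.96 × 0.0510/0.0798 = 1.25, giving 21.0% against 21.9% simulated. At τ = 0.05: 1.96 × 0.0504/0.0585 = 1.69, giving 9.1% against 8.7%.

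**Would a small-sample critical value alone suffice?** No. With t on 10 degrees of freedom (2.228) and the same standard error at τ = 0.10, 2.228 × 0.0510/0.0798 = 1.42, which still gives about 15%.

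**Conditional point.** With logit(p) = b0 + b1·arm + b2·t + b3·arm·t, the arm log odds ratio at time t is b1 + b3·t. With t in months from commencement, b1 is the effect at t = 0, b1 + 4.5·b3 the effect at mid-trial, and b1 + 9·b3 the effect at the end. As an illustration, let the odds ratio grow log-linearly from 1 to 4. Then b3 = ln 4/9 = 0.154, the mid-trial odds ratio is exp(4.5 × 0.154) = 2, and exp(b1) = 1. The 1 follows from the assumed starting point; it only shows what b1 measures.

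**The case against.** **The random structure is inferred.** The article does not write intercept or only, and a fuller protocol or SAP could add a random slope. This stands as a limit on certainty. But the article does commit itself to one random effect for hospital and to a test made by adding one term to that model. On the ordinary reading the two do not fit each other, and a better test is cheap.

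**The size has no anchor.** No slope SD is given, and at 0.03 per month or below the inflation is negligible. This stands. The intercept SD of 0.91 gives a scale for τ × 9, but it is no evidence about slopes. Hence a range and not one figure.

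**Three stronger readings are tempting and not supported.**

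- A reader might infer that hospital differences are turned into an apparent intervention effect. They are not: the interaction estimate is unbiased, and the fault lies in its stated precision.
- A reader might infer that the primary effect will be reported at day zero. The covariate list for the primary comparison has no interaction, which comes afterwards as a separate examination of trend. The harm arises only if the arm effect is taken from the interaction model.
- A reader might infer that the trial's main question is affected because the background speaks of more rapid translation of policy. The primary objective and outcome concern correct classification and treatment as a proportion, not speed. The trend test is a supporting analysis.

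**Conclusion.** The concern holds for the trend test as stated. If hospitals differ in speed of uptake, the arm-by-time test is anti-conservative: about 5% to 6% false positives at a slope SD of 0.03 log-odds per month or below, about 9% at 0.05, about 22% at 0.10 and about 37% at 0.20. At 0.10 the true SD of the estimate is about 1.6 times the reported standard error (0.080/0.051).

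This rests on reading the single random effect as a random intercept, on assumed slope SDs, and on a latent-scale ICC of 0.2. The day-zero point is exact algebra, but it matters only if the interaction model supplies the reported arm effect, which the article does not say it will. No error in the main-effects primary comparison is shown. This is a worthwhile, inexpensive improvement to a supporting test.

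**What to change.** 1. For the trend test, add a hospital random slope for time and judge the interaction on about 10 degrees of freedom. Alternatively, estimate a slope in each hospital and compare the 12 slopes by t-test or permutation; a permutation test should draw only on the allocations admitted by the restricted randomization.
2. Label the trend test secondary.
3. State that the primary arm effect comes from the model without the interaction. If an arm effect is ever reported from the interaction model, centre time at mid-trial or report the arm contrast averaged over the nine months.

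The cost is one extra variance term, or a two-step analysis, and a sentence of text. No new data are needed. The downside is a wider interval for the trend difference. With 12 hospitals a random-slope variance may be poorly estimated, in which case the comparison of hospital slopes is the simpler choice.

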#### Monitoring

A formal data monitoring committee was not needed in this trial for the following reasons: the patients meeting the inclusion criteria were non-critical (any danger sign of illness or diagnosis with comorbid illness requiring intravenously administered antibiotics were excluded) and patients were treated for a short time period with amoxicillin, a well-characterized and relatively safe drug known for not having harmful effects in the pediatric age group. Furthermore, the study was on adoption of a national policy recommending amoxicillin use. The primary aim of the interim analysis was to determine whether the minimum sample size required in the study was recruited by 6 months with the possibility of extending the trial for a 3-month period if this was not achieved. This interim analysis was conducted by a statistician blinded to the trial arm allocation.

### Ethical considerations

Scientific and ethical clearance to conduct the trial was obtained from the Scientific and Ethics Review Unit of the Kenya Medical Research Institute. The approval is updated annually and provided for the establishment of the CIN and the conduct of this specific trial within it, and provides for the use of de-identified patient data, obtained through retrospective review of medical records without individual informed consent, for the purposes of service evaluation and implementation research.

## Discussion

The implementation gap that arises from failure to move research findings to practice has been described extensively but such descriptions are rarely followed by deliberate efforts to narrow this gap in low-income settings. This study conducted during a nationwide changeover in childhood pneumonia treatment recommendations is an attempt to explore alternative ways of augmenting the already documented, but modest, effect of feedback on health worker performance in providing care to address this translation problem [4]. Randomized trials within collaborative networks have been conducted in developed countries but, to the best of our knowledge, the current randomized study, implemented in real time during a health policy change, and also based within a pediatric network is novel in low- and middle-income countries [20, 21]. At the global level the findings of this trial should provide timely contributions to the ongoing discourse on how best to optimize the effect of feedback on professional practice and health care outcome [6].

The pragmatic approach to addressing public health questions is increasingly being used because of its ability to demonstrate efficacy of interventions in real-life settings. Specific strengths of the intervention delivered here are the theory-based process for the design of both the network platform and feedback intervention, representation of diverse contexts of the health system through the range of facilities in the trial, and the reduced selection bias associated with randomized allocation to limit selection bias [9, 22–24].

Among the limitations of the trial is the relatively limited number of clusters. This may limit our ability to detect effects and may raise concerns as to the external validity of any findings. It is important to note that most cluster trials in health conducted in low- and middle-income countries to date have involved randomization of communities and hospitals have rarely been used as randomization units. Additionally, there are issues related to the delivery of effective feedback that deserve attention but which this study could not address. These questions include, but are not limited to, the ideal duration of feedback interventions, and alternative suggested key components of feedback that could enhance performance but that were not examined in this trial [4]. In our case, the duration of our intervention was informed by sample size considerations (power, significance level, effect size), and the participating facilities’ pediatric workloads. Inefficiencies may occur if the duration determined under these assumptions is considerably longer than the ideal duration of feedback. Conversely, a short intervention duration might omit the effect of feedback that is lesser in magnitude but still useful at a system level. Providing evidence to address these issues will require continued methodological developments, possibly involving adaptive designs to suit the dynamic nature of feedback interventions.

### Trial status

Ongoing.
